### Strategies to improve adherence to interventions {11c}

Improving treatment adherence from participants is a built-in feature of psychotherapy. There are two types of adherence in this project: (1) that participants show up for their appointments and (2) that they adhere to the prescriptions from the therapist in between sessions. While both types are important, the following paragraph is focused on the second type of adherence. During the study, patients will report a written overview of sleep and psychopathology symptoms (depending on assigned group). Therefore, any lack of or change in the level of adherence to treatment will be easily detected, and the therapist will be readily able to address these issues in the therapy session.

Measures to improve protocol adherence from the therapists will also be undertaken: to ensure treatment fidelity, 1 session with each patient will be recorded and assessed by an impartial therapist/supervisor. Furthermore, the filmed therapy session is used to provide supervision to the therapist in the active intervention group.

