**Methods:**

Sixty patients diagnosed with treatment-resistant schizophrenia and comorbid sleep disturbance will be included in this randomized intervention study. Included patients will be randomized to 8–10 sessions of psychotherapy with either CBT-I (active intervention) or regular CBT (active control) following baseline. At baseline and 12-week follow-up, patients will be assessed with clinical interviews (Positive and Negative Syndrome Scale), self-reported measures (e.g., Insomnia Severity Index), and polysomnography. The 24-week follow-up will include the same assessments apart from polysomnography. The active intervention group will receive an individual course of treatment with CBT-I focused on the patients’ sleep patterns, while the active control group will receive an individual course of treatment with standard cognitive behavioral therapy (CBT) focused on patients’ psychopathology. It is hypothesized that while both groups will show improvements on central outcome measures, CBT-I will show greater improvements in sleep disturbances. Further, it is hypothesized that the improvement in sleep disturbances will correlate with an improvement in positive symptoms. Lastly, it is anticipated that the CBT-I group will show objective improvements in sleep architecture, such as sleep latency, wake after sleep onset, sleep efficiency, and total sleep time, compared to the CBT group.

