## Interventions

### Explanation for the choice of comparators {6b}

To test the efficacy of CBT-I, we compare it to regular CBT with a focus on patients’ psychopathology. CBT in general is an evidence-based treatment for treating several types of symptoms in a long range of psychiatric illnesses [8], including schizophrenia [9, 33–35]. In Denmark, CBT is recommended as a first choice of psychotherapeutic intervention for schizophrenia by the Danish Health Authority [36]. No significant difference in RCTs has been found between CBT and other psychotherapies in patients with schizophrenia; however, patients receiving CBT were more satisfied with the intervention, as measured by adherence to treatment [37]. There is generally a lack of evidence of efficacy for other psychotherapeutic interventions in schizophrenia, making CBT the most obvious choice of comparison for CBT-I. CBT-I has also shown to be effective in treating sleep disturbances in a schizophrenia population [2, 16–18] as well as in other psychiatric illnesses [14, 15]. CBT-I is the first-line intervention for insomnia issues across conditions. Therefore, it seems appropriate to compare CBT-I to CBT.

In pharmacological research, the preferred option for trials with a superiority design is to use active control in lieu of placebo control [38]. Meanwhile, authors of a recent review agree that all trial designs are relevant to psychiatric research [39].

Active control groups are often used in RCTs in mental disorders research, and a recent meta-analysis found that groups receiving active control treatment showed a small improvement over those receiving placebo treatment, although this was not found in the trials on schizophrenia included in the meta-analysis [40]. In psychotherapy research, the evidence for active control over placebo control is murky. Expectation effects in psychological interventions are only partly eliminated by an active control group [41]. However, we address expectancy and placebo effects by changing only the focus of the intervention in each group, while using the same therapeutic techniques. Furthermore, by offering two evidence-based interventions and presenting both as such, the expectancy effects are mitigated.

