### Intervention description {11a}

Included patients will be randomized 1:1 to CBT-I with a specific focus on sleep or regular CBT with a specific focus on patients’ psychopathology and related difficulties. The interventions are delivered by two different psychologists with similar experience in the field.

Patients randomized to the CBT-I arm will receive a manualized intervention, specifically adapted for individuals with severe mental illness and sleep disturbances. The intervention is delivered individually over 8–10 sessions at UCS, scheduled approximately once per week across a 12-week period. The duration of sessions varies according to the treatment phase:Session 1 (Initial assessment): 60–120 minSession 2 (Treatment initiation): 60–120 minSessions 3–8 (Titration and relapse prevention): 45–60 min each

The extended duration of the first two sessions is necessary to allow for comprehensive assessment, individualized treatment planning, and thorough patient education.

The treatment protocol follows a Danish CBT-I manual developed for the COSTS project, which follows the general structure of previous manuals [42]. The first session includes a comprehensive assessment of sleep problems, confirmation of inclusion criteria, and introduction to the sleep diary, which patients are instructed to complete daily throughout the intervention. The sleep diary is used both for baseline assessment (between the first and second session) and as an ongoing tool to guide individualized treatment adjustments.

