Core components of the intervention include:SRT: Based on the patient’s average TST from the sleep diary, an initial sleep window is set, with a minimum time in bed (TIB) of 5 h. Bedtime and rise time are fixed to strengthen circadian rhythms. Each week, the sleep window is titrated according to SE: if SE ≥ 85%, TIB is increased by 15 min; if SE is 80–84%, TIB is unchanged; if SE ≤ 79%, TIB is reduced by 15 min. Napping is discouraged throughout the intervention.SCT: Patients are instructed to go to bed only when sleepy, use the bed only for sleep and intimacy, leave the bed if unable to sleep after approximately 20 min, and maintain a consistent wake time regardless of sleep duration.Cognitive restructuring: The intervention targets unhelpful beliefs and worries about sleep, using cognitive techniques to challenge and modify maladaptive thoughts.Sleep hygiene and psychoeducation: Patients receive education on factors affecting sleep (e.g., caffeine, light, exercise), and are encouraged to optimize their sleep environment and routines.Relapse prevention: The final sessions focus on consolidating gains and developing strategies to prevent relapse.

The therapist follows a structured session plan, and adherence to the manual is monitored through continuous supervision by a senior clinical psychologist. The intervention is designed to be reproducible and evidence-based, following current recommendations for CBT-I [43].

The regular CBT intervention is delivered in a format identical to CBT-I. The structure, frequency, and duration of sessions are matched across both arms.

The primary difference is the therapeutic focus: regular CBT targets the participant’s psychopathology and related functional challenges, rather than sleep. Core components include psychoeducation, cognitive restructuring, behavioral experiments, coping skills training, and relapse prevention, with content individualized according to the participant’s needs.

Participants in the regular CBT arm complete a symptom log analogous to the sleep diary used in CBT-I, focusing on relevant psychiatric symptoms and coping behaviors. This log is reviewed in each session and guides the therapeutic process. This approach ensures both groups receive equivalent structure and intensity, with the main distinction being the content and focus of the intervention.

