### Plans to promote participant retention and complete follow-up {18b}

Longitudinal follow-up data are important in clinical trials [57, 58]. Generally, issues with the collection of follow-up data can be summed up in the following categories: (1) unable to contact, (2) unable to complete, (3) refusing, and (4) unable to locate [57]. The loss of follow-up data due to subject attrition is a frequent cause of loss of statistical power or increased risk of bias, which minimizes the generalizability and validity of a clinical trial [57, 59]. Consequently, a robust plan for obtaining follow-up data is important. At the initial assessment, we focus on building rapport and positive interactions between participants and clinicians. This fosters participants’ commitment to both the project and staff [57]. We will build rapport through genuine interest in participants’ issues, history, and potential questions regarding project participation. Prospective participants are informed about the project’s goals, the importance of completing participation, and the personal benefits of participation. These strategies may raise the level of adherence throughout our study [59]. Obtaining accurate personal and demographic data is important in locating and contacting participants during the participation period. Furthermore, at the initial assessment, we will also schedule approximate dates for gathering follow-up data. Having scheduled appointments should increase the likelihood that participants will attend both follow-up sessions. Likewise, after participants have been assigned to a treatment group, the therapist in each group will send written reminders the day before each scheduled therapy session. A strong and continuous focus on overcoming these barriers should maximize the number of participants that complete the follow-up assessments.

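### Therapist is tied to arm, and film-based supervision is assigned only to the CBT-I therapist in the text, so the arms differ in more than focus

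*Protocol article*

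**What the plan says.** On who treats, Intervention description {11a} states: "The interventions are delivered by two different psychologists with similar experience in the field". The retention section {18b} says that "the therapist in each group will send written reminders the day before each scheduled therapy session".

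On filming and supervision, the adherence section {11c} says that "1 session with each patient will be recorded and assessed by an impartial therapist/supervisor", which covers both arms. It then adds that "the filmed therapy session is used to provide supervision to the therapist in the active intervention group". The abstract's Methods paragraph fixes that label by randomising patients to "either CBT-I (active intervention) or regular CBT (active control) following baseline". Separately, the part of {11a} that describes CBT-I says that "adherence to the manual is monitored through continuous supervision by a senior clinical psychologist". The description of regular CBT that follows does not repeat this.

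On what distinguishes the arms, the comparator rationale {6b} says "we address expectancy and placebo effects by changing only the focus of the intervention in each group, while using the same therapeutic techniques". The description of regular CBT in {11a} is more cautious. It says that session structure, frequency and duration are matched, and concludes: "This approach ensures both groups receive equivalent structure and intensity, with the main distinction being the content and focus of the intervention".

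**The concern.** A difference between arms can be credited to the content of CBT-I only if the other features of delivery are alike or vary independently of arm. Here two of them move with arm.

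The first is the person. With one therapist per arm, skill, warmth and alliance are part of the treatment contrast.

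The second is supervision. Feedback on filmed sessions is a quality input, and the text provides it to the therapist whose arm is hypothesised to win.

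The primary outcome is the Insomnia Severity Index (ISI) at 12 weeks. It is self-reported, and most of the study is unblinded; external rating is described for the PANSS interviews, not for the ISI. A better or better-supported therapist could therefore move the primary outcome directly. Of the two features, supervision has a predictable direction, towards CBT-I. The difference between persons could go either way.

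**Working it through.** **Step 1: therapists per arm.** Section {11a} gives two psychologists for two interventions. Section {18b} uses the singular, one therapist in each group. Section {11c} uses the singular for the active arm. No one sentence states one therapist per arm, but nothing suggests that either psychologist works in both, and this is the natural reading of the three together. The therapist indicator then equals the arm indicator. Therapist variance cannot be estimated, and neither a model term nor a larger sample separates it from treatment. This does not depend on any assumed figure.

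**Step 2: supervision, side by side.**

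| Feature | CBT-I | Regular CBT |
|---|---|---|
| One session per patient filmed and assessed | yes | yes |
| Film used to supervise the therapist | stated | not stated |
| Continuous supervision by a senior psychologist | stated | not stated |
| Structure, frequency, duration of sessions | reference | stated as matched |

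The second row carries the point. A sentence covering every patient is followed at once by one that names a single arm.

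**Step 3: set against the claims.** Section {6b} says that only the focus changes. Person and, as written, supervision change too, so the two sections conflict. The matching claim in {11a} covers structure, frequency and duration, and calls focus the main distinction, so it is not contradicted.

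**Step 4: an illustrative size for the therapist term.** The plan gives no figure for therapist variation. The inputs are:
- m = 24 evaluable patients per arm, a target difference of 4 ISI points and 80% power at alpha 0.05, all from Sample size {14}.
- A two-sided test, which is an assumption.
- An SD s, which the article does not state. Solving the two-sample t-test (46 df) backwards gives about 4.84. Check: standard error = 4.84 × √(2/24) = 1.40, and 4/1.40 = 2.86, which gives 80% power.
- An intraclass correlation (ICC) of 0, 0.01, 0.02 or 0.05. This is an assumption and is not in the documents.

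If the two therapists are regarded as random draws from a population of therapists:
- variance as analysed = 2s²(1 − ICC)/m
- variance for a claim about the therapies = 2s²(1 − ICC)/m + 2 × ICC × s²
- ratio of standard errors r = √(1 + m × ICC/(1 − ICC))
- SD of the difference between two therapists = s × √(2 × ICC)
- actual type I error = 2 × [1 − F(c/r)], where F is the reference distribution and c its two-sided 5% critical value

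| ICC | r | SD of therapist difference (ISI points) | Type I, normal | Type I, t with 46 df |
|---|---|---|---|---|
| 0 | 1.00 | 0 | 5% | 5% |
| 0.01 | √1.242 = 1.11 | 0.7 | 7.9% | 7.7% |
| 0.02 | √1.490 = 1.22 | 1.0 | 10.8% | 10.6% |
| 0.05 | √2.263 = 1.50 | 1.5 | 19.3% | 18.7% |

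Both reference distributions round to 8%, 11% and 19%. The ratio and the error rates do not depend on s; the therapist difference in ISI points does. Since r grows with m, the inflation is smaller if fewer patients are treated.

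**Step 5: supervision.** No figure can be derived for its effect. Only its likely direction can be stated.

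**The case against.** The other side has several good points.

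**Disclosure and mitigation.** The article says openly that two different psychologists deliver the therapies and that their experience is similar. The CBT-I arm is manualised. Separate therapists per arm also guard against contamination, since the two therapies share cognitive restructuring, psychoeducation and relapse prevention. This stands: the arrangement is defensible in a single-site trial, and the true therapist effect may be small.

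**No supervision for the control therapist.** A reader might infer that the CBT therapist receives none. The text does not say so. It names one arm and is silent on the other, this is a condensed article, and regular CBT is said to share the format of CBT-I. What stands is that, as written, film-based supervision is provided for one arm.

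**Matched delivery.** A reader might also infer that the matching claim in {11a} is false. It is not, because it never covers the person or the supervision. The conflict lies with the word only in {6b}.

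**Error rate of the planned test.** It is tempting to say that the true false-positive rate is 8% to 19% and that the confidence interval is too narrow. The documents do not support this as a fact. The figures need an assumed ICC and a view of the two therapists as random draws. For the contrast as delivered by these two people, this term does not inflate the ordinary test. The issue is attribution to the therapies, and wider application, rather than an error in the planned analysis.

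**Conclusion.** The point holds as a flaw of attribution and a correctable asymmetry. Confounding of therapist with treatment is structural, given the natural reading of one psychologist per arm. The supervision difference is in the text as written, and its likely direction favours the superiority hypothesis on a self-reported, unblinded outcome. Together they contradict the statement that only the focus of therapy changes.

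The size is not known. The range of about 8% to 19% holds only for assumed ICCs of 0.01 to 0.05, 24 patients per therapist and therapists taken as random draws; an ICC of 0 gives the nominal 5%. The trial remains interpretable as a comparison of two therapies, each as delivered by one therapist. It does not support crediting a difference to focus alone.

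**What to change.** 1. Amend {11c} so that film-based supervision is given to both therapists on the same terms, or to neither, for all remaining patients. Films are already made and assessed in both arms. At 12 January 2026, 5 of the planned 60 patients had been included, so about 55 could still be treated under equal conditions. The cost is modest supervisor time if both receive it, and a small change in delivery between the first patients and later ones, to be recorded with its date.
2. In {6b}, replace the statement that only the focus changes with one that acknowledges different therapists. If supervision already is equal in practice, say so in {11c}. The cost is wording only.
3. Limit the conclusion to the two therapies as delivered by one therapist each, and state the nesting of therapist in arm as a limitation. The cost is wording only.

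A sensitivity table over assumed ICCs is not needed, because trial data could not inform it. Having both psychologists treat in both arms is not required either, since it would exchange confounding for contamination.

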### Relevant concomitant care permitted or prohibited during the trial {11d}

Patients will continue their regular psychopharmacological treatment and attend visits with their regular care team at the referring outpatient clinic. Substantial changes in antipsychotic medication or hospital admittance lasting ≥ 7 days will result in exclusion from the study.

### Provisions for post-trial care {30}

Not applicable, no provisions for ancillary and post-trial care.

### Outcomes {12}

The primary outcome is improvement of the individual ISI score after 12 weeks. Secondary outcome measures are ISI score after 24 weeks and changes in PANSS (both total and subscale scores) [44], Global Assessment of Functioning (GAF) [45], WHO Well-Being Index (WHO-5) [46], Functioning Assessment Short Test (FAST) [47], Personal and Social Performance Scale (PSP) [48], the Process of Recovery Questionnaire (QPR) [49], the Treatment Expectation Questionnaire (TEX-Q) [50] and PSG. All outcomes are measured at baseline, after 12 weeks, and at 24 weeks, except for PSG, which is only measured at baseline and after 12 weeks.

### Participant timeline {13}

The inclusion period will be November 2024–December 2026. Patients included in the study will go through baseline assessments of approximately 3 h, including obtaining informed consent, randomization to intervention, and attachment of PSG equipment. Within two weeks of signing informed consent, the participant will be summoned for the first psychotherapy session in a course of 8–10 individual sessions. The sessions will take place over a period of approximately 12 weeks. Within two weeks of the final psychotherapy session, participants will be summoned for 12-week follow-up assessments, which are identical to the baseline assessments. 12 weeks later, participants will be summoned for a 24-week follow-up, which includes the same battery apart from the PSG. See Fig. 2 for an overview of visits, assessments, and interventions.

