### Trial design {8}

This is a 12-week non-blinded randomized controlled trial (RCT) with a superiority framework. Patients will be randomized 1:1 using a block randomization regimen with variable block sizes (2, 4, and 6), which is done to achieve equal sample size in different groups over time [30]. For a flowchart of the trial, see Fig. 1.

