## Data collection and management

### Plans for assessment and collection of outcomes {18a}

#### Assessment and collection of data

The following instruments will be implemented in the study:ISI is a brief seven-item questionnaire designed to measure perceived as well as changes in levels of insomnia, which has been thoroughly validated [25]. It includes items pertaining to nighttime impairment, such as trouble getting to sleep, staying asleep, and early morning awakenings, and daytime impairment, such as satisfaction, daily functioning, noticeability, and worries related to sleep patterns. Internal reliability, as measured by Cronbach’s coefficient alpha, ranged from 0.76 to 0.78 at baseline and follow-up evaluation. Concurrent validity, as measured by Pearson’s *r* coefficient, ranged from 0.07 to 0.91 across several information sources at baseline and follow-up. These results generally show a significant correspondence between patients’ self-perceived insomnia severity and that obtained from significant others and clinicians [25].PANNS is a semi-structured interview based on 30 items developed to assess the positive, negative, and general psychopathological symptoms of patients suffering from schizophrenia [44]. It has been extensively used in both clinical and research settings to measure and monitor the development of symptoms in schizophrenia. Internal reliability, as measured by Cronbach’s coefficient alpha, was 0.73, 0.83, and 0.79 for the Positive Scale, Negative Scale, and General Psychopathology Scale, respectively. Criterion-related validity (composed of discriminant and convergent validity), as measured by Pearson’s *r* coefficient, generally showed that the subscales of PANSS tend to correlate positively with related constructs and negatively with unrelated constructs. An overview of correlations can be seen in Kay et al. [44].GAF is a transdiagnostic rating instrument developed for objectively assessing the severity of psychiatric illness as it relates to the level of psychological, social, and occupational functioning [45]. This is rated in a single score ranging from 0 to 100 in 10-point intervals, which makes GAF an easy and quick tool to assess the level of functioning. GAF has shown high inter-rater reliability of 0.88 [48].PSP is a semi-structured interview developed to assess functioning in four separate dimensions for patients suffering from schizophrenia [48]. The four dimensions are socially useful activities, personal and social relationships, self-care, and disturbing and aggressive behaviors. This makes PSP a more in-depth instrument for assessing the level of functioning, which is an important variable in schizophrenia research. Inter-rater reliability for this instrument ranged from 0.68 to 0.90 across different occupations, professional backgrounds, and numbers of years working in mental health care [48].FAST is a 24-item instrument administered as a short interview designed to assess challenges in daily functioning in psychiatric patients, which is centered around six domains: autonomy, occupational functioning, cognitive functioning, financial issues, interpersonal relationships, and leisure time [47]. FAST has been demonstrated to have excellent internal consistency (Cronbach’s alpha = 0.89) and concurrent validity through a moderate positive correlation with the Brief Psychiatric Rating Scale and a strong negative correlation with the GAF scale [51].WHO-5 is a brief 5-item self-report measure used to assess levels of subjective psychological well-being, which is one of the most widely used questionnaires in this area [46]. Across several samples, WHO-5 has been shown to have excellent internal consistency with Cronbach’s alpha ranging from 0.83 to 0.95 [52]. Furthermore, WHO-5 has robust enough validity to warrant use as a well-being rating scale in clinical trials [46].QPR is an instrument used to assess the concept of recovery in psychiatric patients recovering from psychosis, which consists of two subscales, namely intrapersonal and interpersonal [49]. The revised version used in the present study is a 15-item instrument, which has been shown to have excellent internal consistency at a Cronbach’s alpha of 0.89 and a convergent validity at a Pearson’s *r* of 0.73 [53].TEX-Q is a 15-item generic instrument to assess treatment expectations in a multidimensional manner [50]. The overall scale has shown good internal consistency at Cronbach’s alpha = 0.79 with the subscales ranging from 0.71 to 0.91, while the test-retest reliability (as measured by Pearson’s *r*) was high for the overall scale (Pearson’s *r* = 0.76, *p* < 0.001) and ranging from *r *= 0.60 to 0.84, *p* < 0.001 for the subscales, except for the process subscale (*r* = 0.39, *p* = 0.026) [50].PSG is a comprehensive overnight sleep study that records multiple physiological parameters, including brain activity, eye movements, respiratory effort, airflow, and oxygen saturation [27, 54]. It measures sleep stages, breathing patterns, and limb movements to diagnose and evaluate sleep disorders such as sleep apnea, narcolepsy, and parasomnias [55]. In research, PSG is the gold standard for assessing sleep architecture and treatment outcomes. PSG demonstrates high validity and test-retest reliability for key sleep parameters, especially in controlled laboratory settings [56].

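### As written, the baseline PSG is recorded after open allocation; the session-1 eligibility check and the dating of the 12-week visit also need tightening

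*Protocol article*

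**What the plan says.** **Order at baseline.** Participant timeline {13} describes one set of baseline assessments of about 3 hours, "including obtaining informed consent, randomization to intervention, and attachment of PSG equipment". The section on assessment and collection of data states that "PSG is a comprehensive overnight sleep study that records multiple physiological parameters". The abstract's Methods say that patients are "randomized to 8–10 sessions of psychotherapy with either CBT-I (active intervention) or regular CBT (active control) following baseline". Trial design {8} reads "This is a 12-week non-blinded randomized controlled trial (RCT) with a superiority framework", and the Concealment mechanism section has the patient receive the envelope that names the intervention.

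**Eligibility.** The Eligibility criteria section offers participation to referred patients who meet the criteria. Intervention description {11a} then adds, for the CBT-I arm: "The first session includes a comprehensive assessment of sleep problems, confirmation of inclusion criteria, and introduction to the sleep diary". The CBT arm is said to have an identical format.

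**Timing of the primary outcome.** Outcomes {12} states: "The primary outcome is improvement of the individual ISI score after 12 weeks". The Participant timeline dates the visit differently: "Within two weeks of the final psychotherapy session, participants will be summoned for 12-week follow-up assessments". The first session falls within two weeks of consent, the 8 to 10 sessions take about 12 weeks, and the 24-week visit follows 12 weeks after the 12-week visit. The retention section says that approximate follow-up dates are already set at the initial assessment.

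**The concern.** A baseline value is a safe reference for change only if it cannot be affected by the allocation. If the patient knows the arm before the PSG night, expectation, relief or disappointment can affect that night, and can do so differently by arm. The Objectives contain a between-arm PSG hypothesis on sleep latency, wake after sleep onset, sleep efficiency and total sleep time. PSG is recorded only at baseline and 12 weeks, so no other night could serve as reference.

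A check of inclusion criteria after allocation, by the therapist who delivers that arm, opens a route for patients to leave after randomisation for reasons linked to the arm. The analysis population requires four completed sessions, so anyone who left at session 1 would also drop out of that population.

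A primary visit dated from the last session makes elapsed time depend on how therapy went. The statistical section nevertheless treats baseline, 12 and 24 weeks as fixed occasions.

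**Working it through.** **1. Order of allocation and PSG.**
- Randomisation and attachment of the PSG equipment both belong to the baseline visit of about 3 hours (Participant timeline).
- The recording runs overnight, so it takes place after that visit.
- Randomisation falls within the visit, so the recording follows randomisation. This holds even if the items in the timeline's list are not in time order.
- The allocation is open and the patient is handed the envelope, so the patient knows the arm that night.
- The abstract's natural reading, randomisation once baseline is complete, does not fit this sequence.

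**2. Eligibility.** Patients are screened before participation is offered, and Trial status counts screened patients (10) separately from included patients (5). The session-1 step is therefore a second check, placed after allocation. The section on discontinuing interventions gives worsening of psychotic symptoms as a ground for discontinuation. It gives consecutive missed sessions, substantial antipsychotic changes and longer admissions as grounds for exclusion. Failing the session-1 check is not listed.

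**3. Time of the primary ISI.** Under the timeline, consent and randomisation share a visit, so one clock serves for both.

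Time of visit = (consent to session 1) + (session 1 to last session) + (last session to visit).

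Inputs from the timeline: 0 to 2 weeks, about 12 weeks, and 0 to 2 weeks.
- The plan's own figure: 0 + 12 + 0 = 12 weeks. It is reproduced only when both gaps are zero.
- Latest on the stated course: 2 + 12 + 2 = 16 weeks.
- 24-week visit: 12 + 12 = 24 to 16 + 12 = 28 weeks.

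The session count gives a different course length, because *n* strictly weekly sessions span *n* − 1 weeks:

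| Course | First to last session | 12-week visit | 24-week visit |
|---|---|---|---|
| 8 weekly sessions | 7 weeks | 7 to 11 | 19 to 23 |
| 10 weekly sessions | 9 weeks | 9 to 13 | 21 to 25 |
| Stated course of about 12 weeks | 12 weeks | 12 to 16 | 24 to 28 |

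Week 7 requires session 1 on the day of consent, eight sessions with no slippage, and follow-up on the day of the last session. It is a theoretical extreme. The text gives no visit date for patients who stop therapy early but remain in the study.

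**The case against.** **On the PSG.** The timeline sentence is condensed and is not explicitly a sequence. The flowchart and visit overview are not shown here and may give the order. PSG is an objective measure and a secondary outcome that the plan calls exploratory, and no therapy has begun that night. These points limit the consequence. They do not remove the conflict between the timeline and the abstract, or the fact that the text as it stands puts the recording after allocation. A reader might infer that the baseline ISI is also taken after allocation. The text does not place the questionnaires relative to the envelope, so that is not supported.

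**On eligibility.** A reader might infer that patients will be excluded by arm after randomisation. The documents do not say so: patients are screened first, and no removal is tied to the session-1 check. What stands is a risk that the wording leaves open.

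**On timing.** Assessment at the end of treatment is a defensible choice in a psychotherapy trial, and a fixed date would catch some patients still in therapy. Approximate dates are set at the initial assessment, so the visits are not wholly detached from randomisation. A reader might quote a range of 7 to 16 weeks, but the lower end sets aside the stated course length. A reader might also infer that the arms will be assessed at different times. The plan matches the structure, frequency and length of sessions across arms, and nothing in the document shows such a difference. What stands is that the visit is labelled 12 weeks but dated from the last session.

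**Conclusion.** The PSG point holds and is the main one. Under the timeline as written, every baseline PSG follows open allocation, which conflicts with the abstract. This assumes that the 3-hour baseline is a single visit and that the figures not shown do not say otherwise. The size of any bias cannot be calculated from the document, and it concerns a secondary, exploratory outcome, not the primary ISI.

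The other two points are secondary. The session-1 confirmation is a risk of arm-related exclusion, not a stated procedure. The 12-week ISI falls at about 12 to 16 weeks after consent, and the 24-week visit at about 24 to 28, if courses last about 12 weeks as stated.

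**What to change.** 1. Open the envelope only after the baseline questionnaires, interviews and PSG night are complete, and reword the timeline and the abstract so that they agree. Session 1 may follow consent by up to two weeks, which leaves room. The cost is that allocation is given at a later contact.
2. Move the confirmation of inclusion criteria to before randomisation, or state that the session-1 assessment has no effect on inclusion in either arm. This is a change of wording.
3. Turn the approximate dates set at the initial assessment into target dates counted from randomisation, with the same window in both arms, and apply them also to patients who stop therapy early. The cost is that a few patients may still be in therapy at the visit. If end-of-treatment assessment is what the sponsor wants, relabel the endpoint as post-treatment and state the expected range of weeks.

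Trial status reports 5 patients included by 12 January 2026 against a target of 60, so an amendment now would cover the remaining 60 − 5 = 55. The order in which allocation and PSG took place in the first 5 should be recorded.
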